### Secondary objectives

The secondary objectives of this trial are to compare the two treatment regimen (oral therapy with Repaglinide and insulin therapy with regular insulin) in terms of efficacy and safety.

The efficacy objectives are change in glycaemic control after 12 months of treatment, glycaemic control assessed by glucose profile done monthly (6 values), change in nutritional status and pulmonary function at 12 and 24 months, as well as the need for antibiotic treatments.

The safety objectives are the incidence and quality (mild, severe, other) of hypoglycaemic episodes and adverse events.

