### Randomization

After detailed information by the physicians of the local CF centre, the patient or legal guardian decided to give written informed consent to participate in the study. The trial was open-labelled in order to avoid use of double-dummy technique which would have required an unacceptable increase in the number of injections for the patients. The patients were allocated to the treatment regimen according to a randomisation list generated by a geigy random number table by central fax randomisation. Stratification was conducted according to gender and two age groups (10–15 years, >15 years). Every randomised patient should have been observed for at least 2 years and be included in the final analysis (“intention-to-treat” analysis).

The trial procedures are summarised in the following Table 1.

**Table 1 T1:** Trial procedures

**Visits/months**	**VS**	**V1**	**V2**	**V3**	**V4**	**V5**	**V6**	**V7**	**V8**	**V9**	**End**
		**0**	**3**	**6**	**9**	**12**	**15**	**18**	**21**	**24**	
Informed consent	+										
Selection/exclusion criteria	+										
Randomisation		+									
Inclusion/exclusion criteria		+									
Demographic data	+										
Medical history	+										
Physical examination	+	+	+	+	+	+	+	+	+	+	+
Concomitant illness and medication	+	+	+	+	+	+	+	+	+	+	+
Blood glucose profile			+	+	+	+	+	+	+	+	+
HbA_1c_		+	+	+	+	+	+	+	+	+	+
Pulmonary function		+	+	+	+	+	+	+	+	+	+
IV therapy (antibiotics)		+	+	+	+	+	+	+	+	+	+
Adverse events		+	+	+	+	+	+	+	+	+	+
Hypoglycaemic episodes			+	+	+	+	+	+	+	+	+
Drug dispensation		+	+	+	+	+	+	+	+		

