### Interventions

#### Therapeutic regimen repaglinide

Therapy started with 3 × 0.5 mg Repaglinide before the main meals. If one meal has been skipped or consisted only of carbohydrate-free food, tablet intake was not recommended. Therapy adjustment (dose increase to 3 × 1 mg or dose reduction to 3 × 0.25 mg) occurred basing on blood glucose level measured 2 hours after a meal. The target value should have been 70–160 mg/dl. If the majority of values were above 160 mg/dl, the dose should have been further increased but not earlier than one week after start of therapy. The maximum dose in this study should have been 12 mg (3 × 4 mg). If low blood glucose levels (hypoglycaemia symptoms or blood glucose level below 50 mg/dl) occurred postprandial or before the next main meal, the repaglinide dose should have been reduced (see Figure 1). Asymptomatic blood glucose levels between 50 and 60 mg/dl could have been tolerated. For some patients, different doses before breakfast, lunch and dinner could have been reasonable.

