### Therapy alternatives when reaching discontinuation criterion

a. Insufficient metabolism control during therapy with repaglinide.

Generally, a shift to insulin would have been necessary; doses of 3 injections of regular insulin before meals were recommended. If fasting blood glucose levels had been high, an additional dose of intermediate/long-lasting insulin before going to sleep was advisable. A shift from repaglinide to glibenclamide would have make sense only if allergic reactions to repaglinide occurred. The use of other oral anti-diabetics could not be recommended based on current scientific knowledge.

b. Insufficient metabolic/glycaemic control during therapy with three injections of regular insulin.

Usually a standard intensified therapy of 4–5 injections a day was recommended.

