### Outcome measures

Primary endpoint:

Primary endpoint was the change in HbA1c after 24 months of treatment.

Secondary endpoints:

Secondary endpoints were glycaemic control assessed by mean HbA1C and mean blood glucose profile; change in BMI-Z-score; change in FEV1% predicted and safety assessed by antibiotic therapy, incidence of adverse events, number of hypoglycaemic episodes, all symptomatic hypoglycaemia, hypoglycaemia that necessitates the help of other persons, hypoglycaemia with unconsciousness or coma and number of blood glucose levels below 50 mg/dl in relation to all blood glucose measurements.

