### Power calculation/analysis

Which number of patients was necessary to show a significant difference between therapy strains of 80% power on the one hand and p <0.05 on the other? Retrospective HbA1c data from a database of the CF centre at Medical School Hannover were used. Measurements of n = 132 HbA1c within the first two years after diabetes diagnosis of n = 44 patients older than 10 years at the date of diagnosis resulted in an average value of HbA1c = 5.6 ± 1.5 (average value ± SD). Within a similar group (older than 10 years) but without diabetes n = 763 measurements yielded an HbA1c of 4.6 ± 0.68 (average value ± SD). A difference of 1 (which is in the range of individual variations during treatment especially in youngsters and young adults) between therapy groups was considered relevant [12]. Calculation with *n Query®* of necessary patients for each group was done with these parameters: Two group *t*-test of equal means (equal n’s) 1; Test significance level, α 0,050; 2 sided test; Group 1 mean, μ_1_ 5,600; Group 2 mean, μ_2_ 4,760; Difference in means, μ_1_ - μ_2_ 1,000; Common standard deviation, σ 1,500; Effect size, δ = |μ_1_ - μ_2_|/σ 0,667; Power 80%. Based on the above assumptions the number of patients in each group was calculated as n = 37. Over a treatment time of 2 years, about 30% of patients were assumed to drop out of the study. Therefore, n = 111 patients have been necessary at the beginning of the study to ensure a number of n = 74 remaining patients at the end of the study.

For analysis, the differences of primary parameter HbA1c repeated measures-ANOVA will be applied. The one-sided zero hypothesis (Repaglinide is not worse than insulin) will be dismissed if a p value under 0.05 occurs. The two therapy groups will be compared concerning secondary parameters statistically using the fisher exact test (comparison of discrete events), the Wilcoxon (non-parametrically distributed parameters) and the *t*-test (parametrically distributed parameters). For comparison of drop-outs between the treatment stains a Cox proportional-hazard-ratio model will be applied.

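### Hypoglycaemia is compared under intention-to-treat while repaglinide failures move to insulin; an on-therapy analysis should stand beside the as-randomised one

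*Protocol article*

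**What the plan says.** The Outcome measures section places safety among the secondary endpoints: antibiotic therapy, adverse events, and several hypoglycaemia measures, including "number of hypoglycaemic episodes, all symptomatic hypoglycaemia, hypoglycaemia that necessitates the help of other persons". It gives no rule linking an event to the therapy being taken when it occurred.

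The Randomization section states the analysis principle, labelled intention-to-treat: "Every randomised patient should have been observed for at least 2 years and be included in the final analysis". It makes no exception for safety. Table 1 records hypoglycaemic episodes from month 3, and adverse events from month 0, up to month 24 and the End visit, with no on-treatment limit.

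On the method, the Power calculation/analysis section says: "The two therapy groups will be compared concerning secondary parameters statistically using the fisher exact test", with Wilcoxon and t-tests for other types of variable.

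The section on therapy alternatives covers failure in each arm. For poor control on repaglinide: "Generally, a shift to insulin would have been necessary; doses of 3 injections of regular insulin before meals were recommended". For poor control on insulin: "Usually a standard intensified therapy of 4–5 injections a day was recommended". The article names no move from insulin to repaglinide.

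The safety aim is in the Secondary objectives section: "The secondary objectives of this trial are to compare the two treatment regimen", with the two regimens named there as repaglinide and regular insulin.

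**The concern.** Read together, these rules let a repaglinide failure finish the 2 years on the comparator while still counting in the repaglinide arm. An episode of hypoglycaemia on insulin after the switch, even one with coma, is then a repaglinide-arm event. The opposite misplacement has no stated route, because insulin failures stay on insulin.

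Hypoglycaemia is a harm that either drug can cause. The article expects it on repaglinide too and provides for a dose response: "If low blood glucose levels (hypoglycaemia symptoms or blood glucose level below 50 mg/dl) occurred postprandial or before the next main meal". A comparison that mixes drugs within one arm therefore bears directly on the safety objective. Expressing events per patient-year does not cure this, since a rate by randomised arm still mixes the two exposures. At stake is whether a real difference in hypoglycaemia between the drugs is understated, and whether the few severe events can be read against the right therapy.

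**Working it through.** **The plan's own figure.** The only sample-size figure is for HbA1c: a difference of 1.0, SD 1.5, two-sided 0.05 and 80% power give 36.3 per group by the t-test, rounded up to the stated 37. It reproduces, but says nothing about hypoglycaemia. The article gives no hypoglycaemia rate for either drug, no switching rate and no intensification rate. What follows is therefore illustrative.

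**Assumed inputs.**
- RR: true repaglinide:insulin hypoglycaemia rate ratio, set to 0.5, 1 or 2.
- s: share of repaglinide-arm follow-up spent on insulin. If 10% switch halfway through, s = 0.10 × 0.50 = 0.05. If 30% switch after a quarter of follow-up, s = 0.30 × 0.75 = 0.225. The 30% borrows the article's drop-out figure as an upper proxy; the article does not split drop-outs into switchers and losses.
- g: share of insulin-arm follow-up on intensified insulin, set to 0 or equal to s.
- x: rate on intensified insulin relative to three-injection insulin, set to 1.5 or 2.
- The rate after a switch is taken to equal that on the comparator regimen.

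**Formula.** With the three-injection insulin rate set to 1:

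observed ratio = [(1 − s) × RR + s] / [(1 − g) + g × x]

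**Example.** RR = 0.5, s = 0.225, g = 0: 0.775 × 0.5 + 0.225 = 0.613. With g = 0.225 and x = 2, the denominator is 0.775 + 0.45 = 1.225, and 0.6125 / 1.225 = 0.500.

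| True RR | Switching only (s = 0.05 to 0.225) | Plus equal intensification, x = 1.5 | Plus equal intensification, x = 2 |
|---|---|---|---|
| 0.5 | 0.525 to 0.613 | 0.512 to 0.551 | 0.500 to 0.500 |
| 1.0 | 1.000 to 1.000 | 0.976 to 0.899 | 0.952 to 0.816 |
| 2.0 | 1.950 to 1.775 | 1.902 to 1.596 | 1.857 to 1.449 |

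**Reading the table.**
- Switching alone always moves the ratio towards 1. Whether that flatters or harms repaglinide depends on which drug has the higher rate, which the article does not say.
- Intensification in the insulin arm raises the denominator. With g = s, setting the observed ratio equal to RR gives x = 1/RR. If repaglinide has the lower rate, the two effects cancel exactly when intensification multiplies the insulin rate by the true insulin:repaglinide ratio. A smaller x leaves some dilution; a larger x exaggerates the difference.
- With no true difference (RR = 1), intensification moves the result away from 1.
- Misplacement between drugs stays one-way throughout: events on intensified insulin are still insulin events in the insulin arm. It is the net effect on the contrast that has no fixed direction.

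**The case against.** The strongest objection is that no sentence says post-switch events are charged to repaglinide. This is inferred from a general intention-to-treat statement and a general line on comparing groups. Safety sets and event attribution commonly sit in an analysis plan, which is not shown. This stands as a limit on the claim: the article leaves attribution open, and only its stated default points this way.

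Follow-up after a switch is also unclear. The Power calculation/analysis section says: "Over a treatment time of 2 years, about 30% of patients were assumed to drop out of the study", and plans a Cox model for drop-outs. If patients who switch become drop-outs, few post-switch events are collected. The Randomization section intends the opposite. The article does not settle it, so the point is conditional.

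An as-randomised safety comparison is also a valid comparison of starting strategies, rescue included. Stopping is tied to outcome: the Discontinuation criteria include failed metabolic control and intolerable side effects, so cutting follow-up at the switch is informative. This stands, and it is why the on-therapy analysis should not take first place.

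Two stronger readings are tempting. A reader might infer a bias fixed in one direction for hypoglycaemia and adverse events alike. Intensified insulin can offset or reverse the net effect, and for adverse events in general no drug-specific rates are given, so no direction follows. A reader might also compute a large loss of power. With assumed 24-month incidences of 40% on insulin and 10% on repaglinide, Fisher power at 37 per group falls from 82% to 61% with 30% switching. But 37 is the number left after 30% drop-out, so the same patients are first removed and then put back as switchers. With all 111 randomised patients (about 55 per group), the same example gives 95% falling to 81%. Both versions rest on assumed incidences.

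**Conclusion.** The concern holds in a limited form. If switched patients are followed for 2 years as the Randomization section intends, hypoglycaemia on insulin after a switch counts in the repaglinide arm and never the reverse. This tends to draw the contrast between the drugs towards no difference, and intensified insulin may offset it partly or fully. The size cannot be derived from the document. Over the assumed range, a true ratio of 0.5 appears as anything from 0.500 to 0.613. The documents do not support saying that the safety comparison is wrong as randomised, that repaglinide is necessarily made to look worse, or that adverse events overall are biased in a known direction. This is a cheap improvement: the plan lacks a second view that answers the drug-level safety question in its own objectives.

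**What to change.** State whether hypoglycaemia and adverse events after a stop or switch of the assigned therapy count in the as-randomised comparison, and keep that comparison. Beside it, pre-specify an on-therapy analysis: count events and patient-time on the assigned therapy until it is stopped or switched, and report later events separately under the therapy taken at onset.

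The cost is wording and a modest amount of programming. Table 1 already records concomitant medication at every visit and hypoglycaemic episodes at every visit from month 3, so splitting at the switch should need no new data collection. The Trial status section says analysis is ongoing, so the rule should be written down before hypoglycaemia is compared between arms.

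The downside should be stated with the result. The on-therapy comparison is not protected by randomisation, and censoring at the switch is informative, because patients stop for poor control or side effects. It is to be read together with the as-randomised result, not in its place.

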### Quality assurance

Clinical on-site monitoring in all trial centres was done by personal visits of a clinical monitor according to standard operating procedures of the Interdisciplinary Centre for Clinical Trials (IZKS) Mainz starting 2008. The monitor checked the informed consent forms and reviewed the entries into the case report form (CRF) on the basis of source documents. The physician allowed the monitor access to at all essential documents and provides support to the monitor. The IZKS Mainz assisted the physician to conduct the study according to the protocol as well as to regulatory and ethical requirements.

### Data management

University of Ulm conducted the data management of the trial. All protocol-required information collected during the study had been entered by the investigator, or a designated representative in the CRF. CRF data were entered by University of Ulm into the database. During the study, data were exported into the statistical analysis system and checked additionally for plausibility, consistency and completeness. Based on these checks, queries have been produced. Any missing data or inconsistencies were reported back to the respective site and clarified by the responsible investigator. After all corrections were done, the database was closed and used for statistical analysis. All collected data have been processed according to the German Data Protection Law and handled in strictest confidence.

### Power calculation/analysis

Which number of patients was necessary to show a significant difference between therapy strains of 80% power on the one hand and p <0.05 on the other? Retrospective HbA1c data from a database of the CF centre at Medical School Hannover were used. Measurements of n = 132 HbA1c within the first two years after diabetes diagnosis of n = 44 patients older than 10 years at the date of diagnosis resulted in an average value of HbA1c = 5.6 ± 1.5 (average value ± SD). Within a similar group (older than 10 years) but without diabetes n = 763 measurements yielded an HbA1c of 4.6 ± 0.68 (average value ± SD). A difference of 1 (which is in the range of individual variations during treatment especially in youngsters and young adults) between therapy groups was considered relevant [12]. Calculation with *n Query®* of necessary patients for each group was done with these parameters: Two group *t*-test of equal means (equal n’s) 1; Test significance level, α 0,050; 2 sided test; Group 1 mean, μ_1_ 5,600; Group 2 mean, μ_2_ 4,760; Difference in means, μ_1_ - μ_2_ 1,000; Common standard deviation, σ 1,500; Effect size, δ = |μ_1_ - μ_2_|/σ 0,667; Power 80%. Based on the above assumptions the number of patients in each group was calculated as n = 37. Over a treatment time of 2 years, about 30% of patients were assumed to drop out of the study. Therefore, n = 111 patients have been necessary at the beginning of the study to ensure a number of n = 74 remaining patients at the end of the study.

For analysis, the differences of primary parameter HbA1c repeated measures-ANOVA will be applied. The one-sided zero hypothesis (Repaglinide is not worse than insulin) will be dismissed if a p value under 0.05 occurs. The two therapy groups will be compared concerning secondary parameters statistically using the fisher exact test (comparison of discrete events), the Wilcoxon (non-parametrically distributed parameters) and the *t*-test (parametrically distributed parameters). For comparison of drop-outs between the treatment stains a Cox proportional-hazard-ratio model will be applied.

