## Background

Diabetes mellitus may be present in patients with cystic fibrosis (CF) starting in the second decade of life. The prevalence increases rapidly with increasing age reaching around 30-40% in the fourth decade. As life-expectancy increases in CF, CF-related diabetes (CFRD) will be diagnosed more frequently in the future [1].

Negative consequences of CFRD include: catabolic metabolism, weight loss, more frequent/more severe infections, deterioration of pulmonary function, reduced life-expectancy and diabetic micro vascular complications [2].

Up to date, insulin is the only recommended treatment of CFRD, whether newly diagnosed or not. But no data are available to answer the question if CFRD must always initially be treated by insulin [3]. Several centres report the successful management of CF-related diabetes using oral anti-diabetic drugs at least for some years [4,5]. Oral therapies would be less invasive for a patient group which is highly traumatized by a very demanding pharmaceutical therapy (including antibiotics, pancreatic enzymes, bronchodilators, mucolytic agents) in addition to physiotherapy. Based on an initiative of the German CF-Foundation (Mukoviszidose e.V.), the present study tries to answer the question, whether oral therapy with repaglinide is as effective as insulin therapy in CF patients with early diagnosed diabetes mellitus.

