### Primary objective

The primary objective of this trial is to compare the glycaemic control on oral therapy with repaglinide tid with that on insulin therapy with three daily injections of regular Insulin over 2 years in patients with CF and CFRD.

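### The primary test takes repaglinide not being worse as its null hypothesis, with no margin, so it cannot establish that repaglinide is as effective as insulin

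*Protocol article*

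**What the plan says.** The Background section (and the Abstract in similar terms) gives the motivating question: "the present study tries to answer the question, whether oral therapy with repaglinide is as effective as insulin therapy in CF patients". The formal objective is neutral: "The primary objective of this trial is to compare the glycaemic control on oral therapy with repaglinide tid". It names no type of hypothesis.

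The Power calculation/analysis section then does two different things.

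- **Sizing.** It asks "Which number of patients was necessary to show a significant difference between therapy strains of 80% power" and uses a two-group t-test: "Test significance level, α 0,050; 2 sided test". The inputs are a difference of 1.0 and an SD of 1.5, and the result is 37 per group. The 1.0 is introduced as a difference that "between therapy groups was considered relevant", and is also described as lying within the range of individual variation.
- **Analysis.** HbA1c is analysed by repeated-measures ANOVA, with this rule: "The one-sided zero hypothesis (Repaglinide is not worse than insulin) will be dismissed if a p value under 0.05 occurs".

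No non-inferiority or equivalence margin appears anywhere in the article.

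**The concern.** A test gives evidence against its null hypothesis, never for it. Here the null is the conclusion the study hopes to reach. Only two outcomes are possible: repaglinide is shown to be worse, or nothing is shown. Neither answers whether it is as effective as insulin.

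This is not detail left to an unseen analysis plan, because the article prints the null, its direction, its sidedness and its level. Nor does treating the sentence as a slip rescue it. If the null were meant to be that repaglinide is worse, a one-sided test without a margin would be a test that repaglinide is superior to insulin. That is also not the question.

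What is at stake is the interpretation of the primary result. Under this rule an imprecise trial is more likely to end in non-rejection, the outcome most open to being taken as equal efficacy.

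The change from a two-sided to a one-sided test at the same 0.05 level is a second, smaller inconsistency.

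**Working it through.** **Inputs** (Power calculation/analysis): difference 1.0, SD 1.5, equal groups, n = 37 per group, two-sided alpha 0.05 for sizing, one-sided 0.05 for analysis. Margins below 1.0 are assumptions, shown as a range, because the article states none. Let D = mean HbA1c on repaglinide minus mean HbA1c on insulin; D > 0 means repaglinide is worse.

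**Formulas.** SE = SD × √(2/n), df = 2n − 2. Power is the probability that a noncentral t with noncentrality D/SE exceeds the critical value (the two-sided test adds the opposite tail).

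**1. The plan's own figure.** Two-sided 0.05, D = 1.0: power is 79.7% with 36 per group and 80.8% with 37. The stated 37 reproduces as a two-sided calculation. One-sided at 0.05, power is 79.3% with 28 and 80.6% with 29, so 29 per group would have been enough.

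**2. Effect of the change in sidedness.** With 37 per group and D = 1.0, power rises from 80.8% to 88.4%. The type I error in the tested direction goes from 0.05/2 = 0.025 to 0.05.

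**3. How often the stated test fails to reject, 37 per group.**

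| True deficit D | One-sided 0.05 (as stated) | Two-sided 0.05 (as sized) |
|---|---|---|
| 0.3 | 79% | 86% |
| 0.5 | 59% | 71% |
| 0.75 | 31% | 44% |
| 1.0 | 12% | 19% |

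Fewer completers raise these figures. At D = 0.5, one-sided, non-rejection is 64% with 30 per group and 73% with 20.

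**4. What a non-significant result can conceal.** SE = 1.5 × √(2/37) = 0.349. With 72 df:

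- largest non-significant observed deficit (one-sided 0.05): 1.666 × 0.349 = 0.58
- half-width of the two-sided 95% CI: 1.993 × 0.349 = 0.70 (0.695 before rounding)
- upper 95% limit at that deficit: 0.581 + 0.695 = 1.28

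A result counted as non-significant could thus be compatible with a deficit larger than the 1.0 the plan calls relevant.

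**5. The same sample as a non-inferiority test.** H0: D ≥ margin, one-sided 0.025, true D = 0.

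| Assumed margin | Power with 37 per group | n per group for 80% power |
|---|---|---|
| 1.0 | 81% | 37 |
| 0.75 | 56% | 64 |
| 0.5 | 29% | 143 |
| 0.3 | 13% | 394 |

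**The case against.** The best defence is that the formal primary objective only says that the treatments will be compared, the trial was sized to find a difference, and the Discussion promises a direct between-group comparison. Against that objective a test for repaglinide being worse is coherent. This stands as far as it goes: the defect is a mismatch between the question the study says it is answering and the test it prescribes. It does not remove the mismatch, because the Abstract and Background both ask about equal effectiveness.

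Several stronger readings are tempting, and the document does not support them.

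- **That the plan will report non-significance as equal efficacy.** No section says so. A reader might infer it because, under this null, non-rejection is the only outcome on the favourable side. It is a risk of misreading and not a stated rule.
- **That the one-sided level under-sizes the trial or favours repaglinide.** It does the opposite. It raises power at 1.0 and lowers non-rejection at a deficit of 0.5 from 71% to 59%. It is an inconsistency in error rate only.
- **That the non-rejection percentages are properties of the planned analysis.** They assume a t-test at one time point with the retrospective SD of 1.5. The plan uses repeated-measures ANOVA, and Outcome measures defines the endpoint as change. The SD of change and the within-patient correlation are not given, so the figures are illustrative.
- **That a margin can simply be added before database lock.** Data management describes the closing of the database in the past tense, and Trial status says analysis is under way, in an open-label trial. A margin set now may be post hoc.

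**Conclusion.** The rule is wrong as written for the stated question. The null is the claim to be shown, there is no margin, and no result of the test can demonstrate that repaglinide is as effective as insulin. This conclusion follows from the wording alone and needs no numerical assumption.

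Its size is illustrated, under the single-time t-test with SD 1.5 and 37 per group, by 59% non-rejection at a true deficit of 0.5 and by a non-significant observed deficit of up to about 0.58, with an upper 95% limit of about 1.28.

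The sidedness mismatch is real but secondary; the sample size is not too small because of it.

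The 1.0 should not be taken as a ready-made margin. It was set as a difference to detect, and its acceptability as a permitted loss is nowhere argued.

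**What to change.** **Lead change.** Delete the one-sided 0.05 rule. Report the between-group HbA1c difference from the planned model with its two-sided 95% confidence interval, and state that a non-significant p-value will not be read as equal efficacy. This needs no margin and no new data, and it remains possible while the analysis is in progress.

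**Only if a margin can still be fixed and justified by people without knowledge of the results:** restate the hypotheses as H0: D ≥ margin against H1: D < margin, at one-sided 0.025. Claim that repaglinide is as effective only if the upper limit of the two-sided 95% confidence interval lies below the margin. If 1.0 is proposed, it needs its own justification as a margin.

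**Cost.** A change of wording in the hypothesis and decision rule. The price is that the claim may have to be weaker. The planned 80% power carries over only to a margin of 1.0 and falls to about 29% for a margin of 0.5.
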